### Assessment of recurrence

If recurrence is suspected during follow-up, additional imaging by MRI, CT, PET or US with FNAC will be performed whatever is judged necessary by the attending physician. Examination under general anesthesia is performed if deemed necessary. All recurrences must be confirmed by cytology or histology.

Central evaluation will be done for all regional recurrences in order to determine if the recurrence occurred in an electively irradiated lymph node. The exact site of recurrence will be reconstructed by performing co-registration of the planning CT-scan with diagnostic imaging of the recurrence.

All recurrences in electively irradiated lymph nodes will be reported as a serious adverse event since this is the safety endpoint of this trial.

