### Endpoints

Primary endpoint (toxicity): ‘normalcy of diet’ at 1 year after treatment, measured using the performance status scale for patients with head and neck cancer (PSS-HN) [16].

Secondary endpoint (safety): actuarial rate of recurrence in electively irradiated lymph nodes at 2 years after treatment.

Other endpoints:

Acute toxicity (mucositis, dysphagia and skin reaction).

Late toxicity (with focus on xerostomia, dysphagia and hypothyroidism).

Quality of life (general-, xerostomia- and dysphagia related quality of life).

Recurrence (local, regional, loco-regional and distant).

Survival (overall, disease specific and disease free).

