### Risk assessment of lymph nodes

#### Intervention arm

In the intervention arm, lymph nodes will be classified into three risk-levels and will be treated with a corresponding radiation dose. The FDG-PET-scan will guide risk assessment using standardized methods in order to minimize inter-institutional and inter-operator variations.
*High-risk (macroscopic tumor)*: comprises metastatic nodes that will be identified by (1) positive cytology or (2) necrosis on imaging or (3) SUR_max_ ≥ 2.0.

*Intermediate-risk*: comprises lymph nodes of borderline size having intermediate FDG-uptake and will be identified by (1) summed long- and short-axis diameter ≥ 17 mm and (2) SUR_max_ ≥ 1.5 and <2.0 and (3) cannot be high-risk (e.g. positive cytology or necrosis on imaging). These criteria are based on an in-depth risk assessment on recurrence in 1166 electively irradiated nodes in 264 patients. Not overtly pathologic lymph nodes with a summed diameter ≥ 17 mm had an increased risk to recur after elective treatment (Hazard Ratio: 17.8, 95%CI: 5.7–55, *p* < 0.001) [17].

*Low-risk (microscopic tumor)*: comprises elective lymph node regions defined in the protocol based on tumor site and stage and will be delineated according to published guidelines [20].

Retropharyngeal lymph nodes will be evaluated by traditional means as standardized FDG-PET-guided risk-assessment is not applicable to these nodes.

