#### Control arm

In the control arm, no areas of intermediate risk will be identified. Lymph nodes are either assigned to the high-risk (macroscopic) volume or low-risk (elective) volume by traditional means (positive cytology or necrosis on imaging or short-axis diameter ≥ 10 mm, ≥11 mm for subdigastric nodes).

The FDG-PET-scan may be used in the decision making process by means of visual interpretation.

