### Delineation and margins

For the primary tumor, the gross target volume (GTV_p_) will be delineated by traditional means using information from clinical examination and diagnostic imaging (CT and/or MRI) and will encompass all overtly macroscopic disease. In both treatment arms, a biological target volume (BTV_p_) of the primary tumor is created by means of adaptive threshold iso-contouring based on the FDG-SUR maps [19]. Gross / high-risk lymph node metastases will be delineated separately (GTV_n_).

A clinical target volume (CTV) is created to cover all routes of potential subclinical disease spread.

The GTV_p_ will be expanded by a 3D margin of 10 mm and the GTV_n_ will be expanded by a 3D margin of 5 mm (10 mm in case of extra nodal disease on imaging) in order to create the CTV_high-risk_. The CTV_high-risk_ will be adjusted for anatomical borders in which microscopic disease is unlikely to extend. No CTV expansion will be used for intermediate-risk lymph nodes as extra nodal disease is unlikely in these nodes.

To take patient set-up uncertainties into account, a planning target volume (PTV) will be created by extension of the CTV with a 3D margin of 3-5 mm (according to the participating centers protocols). Additionally, for the high-risk tumor volume an additional PTV_BGTV-high-risk_ will be created by extension of the BTV_p_ and GTV_n_ with a 3D margin of 3-5 mm. Differences in target volumes and dose prescription between the treatment arms are illustrated in Fig. 2.

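### The safety comparison counts recurrences in electively irradiated nodes, but each arm decides which nodes are elective by its own criteria, so an identical node can count in one arm only.

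*Protocol article*

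**What the plan says.** The secondary (safety) endpoint in the Protocol article, Endpoints, is the "actuarial rate of recurrence in electively irradiated lymph nodes at 2 years after treatment". Assessment of recurrence uses the same term for expedited reporting: "All recurrences in electively irradiated lymph nodes will be reported as a serious adverse event since this is the safety endpoint of this trial". Safety assurance uses it again: a log-rank comparison after every fifth such recurrence, against a critical value of 1.728 (nominal one-sided 0.042, overall 0.10).

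Risk assessment of lymph nodes gives the arms different rules.

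- Intervention arm: high risk is positive cytology, necrosis or SURmax of at least 2.0. Intermediate risk is a summed diameter of at least 17 mm with SURmax from 1.5 to below 2.0. Low risk "comprises elective lymph node regions defined in the protocol based on tumor site and stage".
- Control arm: there is no intermediate class. "Lymph nodes are either assigned to the high-risk (macroscopic) volume or low-risk (elective) volume by traditional means", meaning positive cytology, necrosis or a short axis of at least 10 mm (11 mm for subdigastric nodes). In addition, "The FDG-PET-scan may be used in the decision making process by means of visual interpretation".

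Table 1 gives 66 Gy to gross and high-risk disease in both arms, 58 Gy to intermediate-risk nodes (intervention only), and 42 Gy (intervention) or 48 Gy (control) to the low-risk volume. Regional recurrence is listed among the other endpoints. Central review covers every regional recurrence: "Central evaluation will be done for all regional recurrences in order to determine if the recurrence occurred in an electively irradiated lymph node".

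**The concern.** A between-arm comparison of failures needs an event definition that does not depend on the allocated arm. Here a recurrent node counts only if it was elective, and the allocated arm's criteria decide that. The count can therefore differ between arms for the same node with the same outcome.

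The nodes that change class matter to this endpoint. The Intervention arm section reports that nodes not overtly pathologic with a summed diameter of at least 17 mm were much more likely to recur after elective treatment (hazard ratio 17.8, 95% CI 5.7–55). Sample size calculation takes its 5% benchmark from the same cited study.

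The second part is the 58 Gy level. It is one of the two new dose levels under test. The article uses the word elective for the low-risk class and lists the intermediate class apart, so on its wording failures in 58 Gy nodes are not named in the SAE rule or the interim trigger. At stake is what the safety committee sees while the trial runs, and how the final elective-node comparison can be read.

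**Working it through.** **The plan's own figure.** 1 − Φ(1.728) = 0.0420, so the nominal level and critical value agree. The point does not depend on them.

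**Node classes.** Inputs are the criteria in the Intervention arm and Control arm sections, the doses and EQD2 values in Table 1, and nodes that are not retropharyngeal and have no positive cytology or necrosis. The cut is a short axis of 10 mm (11 mm subdigastric). A node at the cut has a summed diameter of at least 10 + 10 = 20 mm, so it always meets the 17 mm criterion. Visual PET reading can change the control class, so these are defaults.

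| Class | Short axis | SURmax | Control | Intervention | Counted, article's wording | Counted, if 58 Gy is elective |
|---|---|---|---|---|---|---|
| a | at or above cut | 1.5 to <2.0 | 66 Gy | 58 Gy | neither arm | intervention only |
| b | below cut, sum ≥ 17 mm | 1.5 to <2.0 | 48 Gy | 58 Gy | control only | both arms |
| c | at or above cut | <1.5 | 66 Gy | 42 Gy | intervention only | intervention only |
| d | below cut | ≥2.0 | 48 Gy | 66 Gy | control only | control only |

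Examples: a 9 × 8 mm node (sum 17 mm) falls in class b at SURmax 1.7 and class d at SURmax 2.2. A 14 × 10 mm non-subdigastric node at SURmax 1.3 falls in class c. Classes c and d count in one arm only under either reading of the term.

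**Dose change, control to intervention (EQD2, Table 1).**
- a: 73 to 60; 13/73 = 18% lower
- b: 45 to 60; 15/45 = 33% higher
- c: 73 to 35; 38/73 = 52% lower
- d: 45 to 73; 28/45 = 62% higher

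**Direction.** Classes b and d take events out of the intervention count. Class c adds events to it. The article gives no class frequencies, so the net effect is unknown.

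**Illustrative size.** Simulation: 100 control and 200 intervention patients, uniform accrual over 4 years, exponential times, 2 years of follow-up, no dropout, a look after every fifth event, stop if z > 1.728, 4000 runs per case. The Monte Carlo standard error is √(0.043 × 0.957/4000) ≈ 0.003 for the first line, and at most about 0.008.

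- 5% vs 5%: 0.043. This is below 0.10 because only about 15 events are expected (100 × 0.05 + 200 × 0.05), hence about three looks. At the first look even five out of five events in the intervention arm give z ≈ (5 − 3.33)/√(5 × 2/9) = 1.58.
- Share in classes b and d, not counted in intervention: at 10%, 5 × 0.9 = 4.5% vs 5%, 0.022; at 30%, 5 × 0.7 = 3.5%, 0.009.
- Share added by class c, counted in intervention only: at 10%, 5 × 1.1 = 5.5%, 0.060; at 30%, 5 × 1.3 = 6.5%, 0.118.

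The 10–30% shares are assumptions. Each direction is run alone, and these nodes are taken to fail equally often at either arm's dose.

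**58 Gy nodes alone.** Suppose failures in low-risk nodes double, and class b nodes (share s of control events) fail at 58 Gy as often as at 48 Gy. The intervention rate is 5 × (2(1 − s) + s) if they are counted and 5 × 2(1 − s) if not. For s = 10%, 9.5% against 9.0%: crossing 0.41 against 0.34. For s = 30%, 8.5% against 7.0%: 0.30 against 0.17. If 58 Gy controls these nodes, nothing is lost.

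**The case against.** Much of the asymmetry is the intervention itself. PET-guided reclassification is the randomised strategy, and the stated objective is worded for electively irradiated nodes, so objective and endpoint agree. A class c node that fails at 42 Gy after losing the boost is the harm the rule should catch; moving class b and d nodes to a higher dose is an intended benefit. The no-difference scenarios set this aside by assuming equal failure at different doses. If class c nodes fail less often at 66 Gy, part of the extra crossing is a true alarm. This stands, and it is why the formal endpoint should stay. It does not make the counts comparable: a class c failure at 66 Gy in control is still left out.

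A reader might infer that recurrences in 58 Gy nodes escape safety monitoring. The documents do not support that. Their exclusion is inferred from usage in a condensed article, and the full protocol may define the term. They may be SAEs under general criteria not shown. They go to central review and count as regional recurrence, which is compared by log-rank test. The safety committee also has a general remit to review trial safety.

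A reader might also infer that the rule favours the intervention. That is not supported either, since the classes work in opposite directions. Pre-treatment ultrasound with cytology, and visual PET reading in control, both make the discordant classes smaller.

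**Conclusion.** The point holds in a limited form. The formal safety count depends partly on the allocated arm's node criteria, and under either reading of the term at least classes c and d count in one arm only. On the article's wording class b does too; if the full protocol treats 58 Gy nodes as elective, class a does instead. It is also correct, on the wording shown, that 58 Gy recurrences are not named in the SAE and interim rules.

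The size is unknown. The simulated ranges (0.01–0.02 or 0.06–0.12, against 0.04) rest on assumed shares, one class at a time, and no dose effect. They show that the matter could be small or noticeable, not which way it goes. This is a reason for a cheap supplement to the safety data. It is no reason to replace the endpoint or to call the interim rule invalid.

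**What to change.** Keep the elective-node endpoint, the 5%/10% benchmark and the 1.728 boundary, and add three things.

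1. Safety assurance: at every look, show the safety committee all regional recurrences by randomised arm, as supporting data with no boundary of their own. Report them beside the elective-node result at the end. This count does not depend on how nodes were classed.
2. Assessment of recurrence: have the planned central review class each recurrent node in both arms by the intervention-arm criteria, from the planning PET/CT and the pre-treatment work-up (retropharyngeal nodes by traditional means, as now). Use that class in a sensitivity analysis of the elective-node comparison.
3. Assessment of recurrence: report recurrences in 58 Gy nodes as SAEs as well.

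The cost is small: one extra field per regional recurrence, one committee table and a few more SAE reports. Central review of all regional recurrences is already planned. Table 2 schedules a planning FDG-PET/CT before treatment, and SUR maps are already used in both arms, where the primary tumour's biological volume "is created by means of adaptive threshold iso-contouring based on the FDG-SUR maps". The event trigger and looks do not change. The drawback is that regional recurrence also contains failures in 66 Gy nodes, which dilutes an elective-dose effect. It therefore supplements the formal rule and does not replace it.

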### Functional assessments

*Salivary gland function* will be evaluated in a part of the participating centers only. Stimulated parotid and submandibular salivary flow rates (sialometry) will be measured using techniques described previously [25, 26]. Samples of saliva collected with sialometry will be analyzed for its composition (sialochemistry).

*Swallowing function* will be evaluated using the water swallowing test [27]. Additional functional performance will be evaluated by the Performance Status Scale for Head & Neck Cancer Patients (PSSH-HN) [16].
*Thyroid gland function* will be evaluated using standard blood analysis measuring the thyroid stimulating hormone and free thyroxin.

### Assessment of quality of life

For evaluation of general quality of life, the EORTC QLQ-C30 and EORTC QLQ-H&N35 questionnaires will be used [28, 29]. Xerostomia related quality of life will be evaluated using the Groningen Radiation Therapy Induced Xerostomia questionnaire (GRIX) [30] and dysphagia related quality of life will be evaluated using the Swallowing Quality of Life Questionnaire (SWAL-QOL) [31].

### Statistical analysis

All analyses concerning treatment effects will be done according to the intention to treat principle. The student’s t-test will be used to compare ‘normalcy of diet’ scores at 1 year after treatment, the primary endpoint of this trial. A Kaplan-Meier estimate will be calculated for the actuarial rate of recurrence in electively irradiated lymph nodes at 2 years after treatment. Actuarial rates on recurrence and survival will be determined by the date of histopathological diagnosis. Differences between the treatment arms will be assessed using the log-rank test.

For each quality of life questionnaire, data will be included in the analysis if a patient filled in the questionnaire at least at start and at one time-point during the study. Differences in quality of life over time between the intervention- and control arm will be analyzed by using a linear mixed model for repeated measurements. Difference in quality of life scores ≥10 points will be considered clinically relevant [32].

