### Study design

This is a multicenter, phase III, single-blinded, randomized controlled trial.

Treatment allocation at randomization will be at a ratio of 2:1 in favor of the intervention arm. Randomization will be balanced for institution, tumor-site, T- and N-stage, and human papillomavirus status using minimization with a random element. Randomization and clinical trial data management is provided by the IKNL clinical research department.

A flow chart giving an overview of the study design is shown in Fig. 1.

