### Sample size calculation

This study was designed to detect a 10-point difference on the PSS-HN ‘normalcy of diet’ score at 12 months after radiation therapy with a power of 90% at a two-sided significance level of 0.05. An average ‘normalcy of diet’ score of 70 is expected after standard treatment. To achieve this significance level with an unequal randomization ratio (2:1), a total of 300 patients needs to be included.

The current rate of recurrence in electively irradiated lymph nodes was estimated to be 5% at 2 years after treatment [17]. An equal rate of recurrence is expected in the intervention arm, despite elective dose de-escalation. A recurrence rate of ≥10% will be considered clinically relevant and unacceptable. This difference can be detected with the number of patients planned for the primary outcome of the study and a one-sided α = 0.10.

The total duration of this trial is estimated to be 6 years (4 years accrual, 2 years follow-up).

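### The primary Student's t-test pools variances under 2:1 allocation, so any interval from it is slightly off if the arms' spreads differ; Welch's test removes this at no cost

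*Protocol article*

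**What the plan says.** The Statistical analysis section of the protocol article names one method for the primary endpoint: Student's "t-test will be used to compare" the 1-year normalcy of diet scores. It does not mention Welch's test or say how the variance is to be estimated, and it specifies no confidence interval for this comparison.

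Under Study design, "Treatment allocation at randomization will be at a ratio of 2:1 in favor of the intervention arm". Under Sample size calculation, "This study was designed to detect a 10-point difference on the PSS-HN" diet score "with a power of 90% at a two-sided significance level of 0.05", a mean "score of 70 is expected after standard treatment", and "a total of 300 patients needs to be included". That gives about 100 control and 200 intervention patients. No SD, common or by arm, is stated, and neither are the limits of the scale.

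**The concern.** In its usual meaning, Student's two-sample test assumes equal variances and pools them. With arms of equal size that assumption hardly matters. At 2:1 it does: the larger intervention arm dominates the pooled variance, while the smaller control arm contributes most of the true variance of the difference in means. If the intervention arm is the less variable, the pooled standard error is too small; if it is the more variable, it is too large.

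Having 100 and 200 patients answers a worry about non-normal scores, because the means will be close to normal. It does not answer this one, because the relative error in the standard error depends on the allocation ratio and the SD ratio, and not on total n. At stake is whether an interval reported for the trial's main result has its nominal coverage.

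**Working it through.** **Inputs from the article.** Difference 10 points; control mean 70, hence 80 in the intervention arm under the design alternative; two-sided α 0.05; power 90%; 2:1 allocation; N = 300, so n₀ = 100 and n₁ = 200.

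**Assumed inputs.** The SDs and a 0-100 scale.

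**The plan's own figure.** Without an SD, 300 cannot be reproduced from the article alone. With a common SD of 25, the control arm needs 1.5 × 25² × (1.960 + 1.282)² / 10² ≈ 98.5, so 99 + 198 = 297, close to 300. Solving back from exactly 300 gives an SD of 25.2 with no dropout, 23.9 with 10% dropout and 22.5 with 20%. An SD of 25 is therefore a reasonable working value.

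**A plausible intervention SD.** If the variance on a 0-100 score scales with mean × (100 − mean), an SD of 25 at mean 70 becomes 25 × √[(80 × 20)/(70 × 30)] = 25 × √(1600/2100) ≈ 21.8 at mean 80.

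**Formulas.**
- True SE = √(s₀²/100 + s₁²/200)
- Pooled variance = (99 s₀² + 199 s₁²)/298
- Student SE = √[pooled variance × (1/100 + 1/200)]
- Ratio r = Student SE / true SE
- Coverage ≈ 2Φ(1.968 r) − 1, where 1.968 is the t quantile on 298 degrees of freedom

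**Example, 25/21.8.** True SE = √(6.25 + 2.381) = 2.938. Pooled variance = (61,875 + 94,762)/298 = 525.6, so Student SE = √(525.6 × 0.015) = 2.808. Then r = 0.956 and coverage ≈ 94.0%.

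| SD control / intervention | True SE | Student SE | r | Student coverage | Simulated: Student | Simulated: Welch |
|---|---|---|---|---|---|---|
| 25 / 25 | 3.062 | 3.062 | 1.000 | 95.1% | 94.9% | 94.9% |
| 25 / 21.8 | 2.938 | 2.808 | 0.956 | 94.0% | 94.1% | 95.1% |
| 25 / 20 | 2.872 | 2.669 | 0.929 | 93.3% | 92.9% | 94.8% |
| 25 / 15 | 2.716 | 2.317 | 0.853 | 90.7% | not run | not run |
| 25 / 30 | 3.279 | 3.483 | 1.062 | 96.3% | 96.4% | 95.1% |

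The simulations used normal data and 20,000 trials per row. With the multiplier 1.96 in place of 1.968, the 25/20 row gives 93.1%.

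**Role of the ratio.** At 150:150, r is 1.000 for each SD pair and coverage returns to about 95%. The 2:1 allocation is what exposes the test.

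**Bounded score.** Simulating a 0-100 score in steps of 10, with means 70 and 80 and SDs 25 and 21.8, gives coverage of 93.6% for Student and 94.8% for Welch. When both arms are drawn from the same distribution (mean 70, SD 25), Student's type I error is 5.1%.

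**Equal means, unequal spreads.** Here the error rate is one minus the coverage: about 6.0% at 25/21.8, 6.8% at 25/20 and 3.7% at 25/30.

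**Power at 25/21.8.** Student: Φ(10/2.938 − 1.968 × 0.956) = 93.6%. Using the true SE, as Welch does: Φ(10/2.938 − 1.960) = 92.6%. At 25/25 both are about 90%.

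**The case against.** The strongest reply concerns the mechanism. The only reason in the article to expect unequal spreads is the treatment effect itself, which moves the mean from 70 towards 80. If treatment leaves the score distribution unchanged, the spreads are equal and the pooled test keeps its level at any allocation ratio. A reader might infer that the test is anti-conservative and will produce false positives. The article does not support that: when the spread differs because of an effect, the null hypothesis is already false. Inflation needs equal means with unequal spreads, which is possible, but nothing in the text points to it. This part of the objection stands.

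A reader might also infer that the plan itself makes unequal spreads likely. It does not. The 10 points are a design alternative, and a smaller SD at the higher mean depends on an assumed ceiling at 100. That stands too, as does the point about size: the assumed 10-point shift costs about one point of coverage, and coverage near 91% needs an SD ratio of about 0.6, which that shift does not give.

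Finally, Student's may be a generic label for any two-sample t-test, and the full protocol may settle the variant. The pooled form is nevertheless the ordinary reading of the one method the article names, so this weakens the point without removing it.

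**Conclusion.** The point holds as a minor, free improvement. The named test, read in its ordinary pooled form, has a biased standard error at 2:1 if the SDs differ, and more patients at that ratio would not help. Under an assumed 0-100 score with SDs of 25 and about 21.8, the standard error is about 4% too small, and a 95% interval derived from the test covers about 94%. If the intervention arm is the more variable, the error goes the other way and the interval is too wide.

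The consequences are limited to interval coverage, about one percentage point of flattered power at 25/21.8, and the error rate for equal means with unequal spreads. It would be wrong to conclude that 300 patients is the wrong number: nothing here bears on that figure. No interval is stated for the primary comparison, so the coverage results apply to any interval that would be derived from the test.

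**What to change.** In the Statistical analysis section, replace Student's t-test with Welch's unequal-variance t-test for the 1-year normalcy of diet comparison, and state that any reported 95% confidence interval for the difference is based on it. If Student's was meant generically, the same sentence resolves the ambiguity before the data are analysed.

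The cost is one sentence. N stays at 300, no data are added, and the power loss when the SDs are equal is negligible. In the simulated scenarios Welch's coverage was 94.8% to 95.1%.
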